## Abstract

During interpersonal emotion regulation, relationship partners mutually regulate each other’s emotional states. Interpersonal emotion regulation occurs at three main timescales: phasic (from several hundred milliseconds to about 10s), tonic (from 10s to 1 hour), and chronic (from weeks to months and years). Prior research has examined interpersonal emotion regulation at only one or two timescales simultaneously. The proposed research will examine variables relating to interpersonal emotion regulation in close relationships across all three timescales. A total of 150 romantic couples will engage in an emotional sharing task, in which they will be instructed to either engage in natural sharing or co-rumination. At the phasic timescale, primary outcomes will be interpersonal synchrony in movements and cardiovascular responses throughout the sharing task. At the tonic timescale, primary outcomes will be changes in mood and emotional appraisals pre- and post-sharing. At the chronic timescale, the study will primarily assess individual differences in relationship quality and dyadic coping style prior to the task, which are expected to shape phasic and tonic patterns during emotional sharing. Our general expectation is that phasic patterns in interpersonal emotion regulation (e.g., movement synchrony) will be meaningfully related to tonic patterns (e.g., mood change), which, in turn, will be meaningfully related to chronic patterns (e.g., relationship quality). More differentiated hypotheses and exploratory analyses are detailed in the protocol. The results of this research will contribute to the integration of interpersonal emotion regulation theories across different time scales.

## Introduction

Within close relationships, partners regulate each other’s emotional states. Such interpersonal emotion regulation is of vital significance for the health and wellbeing of the individual relationship partners, as well as for the quality of their relationship [1–3]. It thus seems important to learn more about the processes that underlie interpersonal emotion regulation within close relationships.

One fundamental aspect of interpersonal emotion regulation is that it unfolds dynamically over time [1,4]. Prior work has distinguished between three main timescales of interpersonal emotion regulation [5–7]. First, the phasic timescale runs from several hundreds of milliseconds to about 10 seconds. Interpersonal emotion regulation at the phasic timescale is mostly nonverbal, and occurs in exchanges of facial expressions, eye gaze, breathing patterns, or whole-body movements [7]. Second, the tonic timescale runs from about 10 seconds to roughly one hour. Interpersonal emotion regulation at the tonic timescale consists of socially meaningful, often verbal exchanges, such as emotional sharing [8], for example during a casual encounter or a psychotherapy session [9]. Third and last, the chronic timescale runs from several weeks to months and years. Interpersonal emotion regulation at the chronic timescale consists of more or less stable patterns of behaviour, which may be driven by personal dispositions (e.g., chronic attachment style [10]) and/or stable relationship characteristics (e.g., dyadic coping styles [11]). Importantly, in this study, the chronic timescale is not assessed longitudinally after the task, but is operationalized through individual and relational characteristics (e.g., dyadic coping and relationship quality) measured before the emotional sharing interaction, which are hypothesized to moderate the effects observed at the phasic and tonic levels.

At any given moment, the functioning of a close relationship is characterized by phasic, tonic, and chronic processes, along with the interplay of these processes. Leading theories on interpersonal emotion regulation primarily focus on one of these time scales. Synchrony [5] focuses on spontaneous moment-to-moment interpersonal alignment of aspects like bodily movements and physiological processes. Theories on emotional sharing [8] take the time frame of a conversation as their focus, and theories on dyadic coping [12] often investigate partners’ coping behaviours over a more extended period of time. To date, research has examined variables relating to interpersonal emotion regulation at only one, or at most two timeframes. In the proposed experiment, we seek to obtain a more comprehensive picture of interpersonal emotion regulation, by examining variables relating to interpersonal emotion regulation in close relationships across all three of the phasic, tonic, and chronic timeframes.

Compared to the effects of the co-rumination manipulation on synchrony, mood and appraisal change, we expect that couples’ relationship quality and their dyadic coping strategies have a much stronger effect on synchrony, mood and appraisal change. Couples with a high relationship quality and constructive dyadic coping strategies will already have employed a range of interpersonal emotion regulation and coping strategies to deal with the problem they are discussing, and therefore these brief episodes of natural sharing or co-rumination will minimally affect their synchrony, mood and appraisal changes. In contrast, for couples with a poorer relationship quality or dyadic coping strategies, the co-rumination manipulation to engage in extensively discussing the sharers problems and negative emotions, will have a greater effect on their synchrony and positive mood change than when they engage in their natural way of emotional sharing, but will still result in minimal appraisal changes.

Prior to the emotional sharing task, we will measure a set of variables related to the chronic timescale: relationship quality, dyadic coping and a range of secondary variables (e.g., attachment style, empathy and perceived social support). During the emotional sharing task itself, we will assess phasic processes in the form of movement synchrony [5] and cardiovascular synchrony [20]. Before and after the emotional sharing tasks, we will measure tonic processes: mood and appraisal changes and a range of secondary variables (e.g., conversation experience, perception of partners’ responsiveness and feelings of closeness with the partner).

The proposed experiment has both confirmatory and exploratory parts. The confirmatory part is based on hypotheses that were explicitly derived from the literature on interpersonal emotion regulation. Because of the complexity of the study, we have grouped our hypotheses according to their respective timescales (see Table 1). More detailed information can be found in *Supplementary 1 in*
S1 File*.*

**Table 1 pone.0323526.t001:** Main confirmatory hypotheses for the three timescales.

Timescale	Hypotheses
*Phasic*	1. Relationship partners will display significant levels of movement and cardiovascular synchrony during the emotional sharing tasks, relative to a relevant baseline level of randomized pseudo-interactions. 2. Compared to natural sharing, co-rumination may be associated with enhanced movement and cardiovascular synchrony.
*Tonic*	3. Emotional sharing will generally make sharers and supporters feel better, leading them to report positive mood changes. 4. Emotional sharing will generally help sharers to reappraise their feelings, leading them to report changes in emotional appraisals. 5. Compared to natural sharing, co-rumination may lead to equal or even more positive mood outcomes, possibly due to increased emotional closeness and perceived support. 6. Compared to natural sharing, co-rumination will be associated with smaller changes in emotional appraisals.
*Chronic*	7. Higher relationship quality and more constructive dyadic coping strategies will be associated with 1) stronger movement synchrony; 2) stronger cardiovascular synchrony; 3) stronger positive mood changes; 4) more emotional appraisal changes. 8. Higher relationship quality and constructive dyadic coping may buffer or attenuate potential differences between co-rumination and natural sharing in: (a) movement synchrony, (b) cardiovascular synchrony, (c) mood responses, and (d) emotional appraisal changes.

Moreover, we will conduct a series of exploratory analyses involving the secondary variables to further inform our understanding of interpersonal emotion regulation within close relationships. These exploratory analyses will probe the intricate connections between relational factors, individual characteristics, emotional sharing and physiological responses. In addition, in a second set of exploratory analysis we will be looking at synchrony in verbal communication: 1) linguistic synchrony; 2) vocal synchrony; 3) facial synchrony. These exploratory analyses are elaborated in Supplementary *1 in*
S1 File.

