## Methods and statistical analysis

### Design

This study has a mixed factorial-experimental nested design. In total, each couple engages four times in the emotional sharing task, twice in the co-rumination and twice in the natural sharing condition. Each participant will twice share a distressing experience and will twice act as supporter. Both aspects will be experimentally manipulated between participants. Measures of mood and appraisal will be nested within participants, while movement and cardiovascular synchrony will be nested within dyads. The chronic variables (i.e., dyadic coping and relationship variables) will be used correlational.

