**Fig 2 pone.0323526.g002:**
[figure not shown]
Photograph of the emotional sharing space and one individual workspace.

In the first phase of the experiment, participants will be asked to rate their mood on the mood adjective checklist (BEF) [24]. Then they will be instructed to generate two personal negative experiences using the Experience-Generation Questionnaire (EGQ) [25]. Subsequently, the Experience Scales (ES) [26] will be used to tap into their appraisal of these two experiences. Next, participants will be fitted with the sensors of the Vrije Universiteit - Ambulatory Monitoring System (VU-AMS). Once the VU-AMS has been set up, participants will be requested to complete the pre-sharing survey.

Subsequently, participants will be provided with instructions for the emotional sharing task, consisting of four dialogues. Upon completion of the entire emotional sharing task, participants will complete a post-sharing survey and the ECG device will be removed. Finally, participants will be debriefed, rewarded, and thanked. Fig 3 shows the whole experimental session. In total, the experiment takes approximately 2 hours, with task instructions taking 10 minutes, device fitting taking 15 minutes, the pre-sharing survey taking 15 minutes, the emotional sharing task for four episodes lasting 60 minutes, the post-sharing survey taking 15 minutes, and the device removal and closure taking 5 minutes.

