#### Tonic timescale.

***Mood change analysis:*** To assess changes in mood over time (Hypothesis 3), we will use linear mixed-effects models (LMMs), treating time (pre vs. post) and condition (co-rumination vs. natural sharing) as fixed effects, and including random intercepts for participants nested within dyads to account for the non-independence of dyadic partners and repeated measurements. This approach enables us to examine overall mood changes without splitting sharers and supporters into separate analyses.

For Hypothesis 5, we will examine whether mood following co-rumination differs from mood following natural sharing using the same LMM framework, focusing on post-sharing mood scores across conditions.

***Emotional appraisal analysis:*** To evaluate changes in emotional appraisals (Hypothesis 4), we will calculate change scores by subtracting the pre-sharing appraisal rating from the post-sharing appraisal rating for each emotional episode. These change scores will then be entered into linear mixed-effects models, with condition as a fixed effect and random intercepts for participants nested within dyads. This approach accounts for within-person and within-dyad dependence and avoids the use of separate t-tests for each condition. Hypothesis 6 will be tested by comparing appraisal change scores between the co-rumination and natural sharing conditions using the same dyadic LMM framework.

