## Discussion

The planned research seeks to comprehensively evaluate interpersonal emotion regulation across phasic, tonic, and chronic time scales concurrently. This research design will allow for the examination of three leading theories of interpersonal emotion regulation—namely, synchrony [5], emotional sharing [8], and dyadic coping [12]. These theoretical frameworks and associated processes have so far not been studied within a single research design. By so doing, the planned research will allow us to examine how moment-to-moment (phasic) processes in interpersonal emotion regulation are related to specific episodes (tonic) of interpersonal emotion regulation, and how these, in turn, are related to more enduring (chronic) patterns in interpersonal emotion regulation.

The planned study -like all research- has limitations. First, the study’s generalizability may be limited due to its inclusion of only Dutch-speaking participants with a limited age range and relationship duration. Replicating the planned study with more diverse samples will be important to test the external validity of the findings. Second, the present study contains an experimental manipulation of one tonic process (i.e., co-rumination), but not of phasic processes (movement synchrony and cardiovascular synchrony) or chronic processes, which are both merely measured. Thus, the present study cannot draw causal conclusions about the role of phasic and chronic processes in interpersonal emotion regulation. Third, the study is limited by its reliance on retrospective self-reports for chronic processes and the potential participant fatigue from completing four emotional sharing conversations. While our within-subject design enhanced comparability across conditions, future studies could consider between-subjects or longitudinal designs to reduce participant burden and allow for more direct testing of chronic interpersonal processes over time.

Despite these caveats, the proposed study will be the first to study processes of interpersonal emotion regulation jointly across phasic, tonic, and chronic time scales. We hope that this study will facilitate the development of an integrated theoretical framework for understanding interpersonal emotion regulation.

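### Hypotheses 3 and 4 claim effects of emotional sharing itself, but nothing unshared is compared, so the plan can test only before-to-after change

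*Protocol article*

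**What the plan says.** Table 1 carries the title "Main confirmatory hypotheses for the three timescales". Its tonic rows include Hypothesis 3, "Emotional sharing will generally make sharers and supporters feel better, leading them to report positive mood changes", and Hypothesis 4, "Emotional sharing will generally help sharers to reappraise their feelings, leading them to report changes in emotional appraisals". Hypothesis 3 predicts a direction; Hypothesis 4 predicts change without one.

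The Design section says that "each couple engages four times in the emotional sharing task, twice in the co-rumination and twice in the natural sharing condition", and that "Each participant will twice share a distressing experience and will twice act as supporter". The article describes no dialogue, person or waiting period without sharing.

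Under Tonic timescale, Hypothesis 3 is analysed in a mixed model with time (pre or post) and condition as fixed effects, sharers and supporters together. Hypothesis 4 uses change scores, formed by "subtracting the pre-sharing appraisal rating from the post-sharing appraisal rating for each emotional episode", in a mixed model with condition as the fixed effect.

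On timing, the Procedure has mood (BEF) rated first, then two negative experiences generated. It continues: "Subsequently, the Experience Scales (ES) [26] will be used to tap into their appraisal of these two experiences". Sensor fitting and the pre-sharing survey follow. Table 2, by contrast, lists both the BEF and the ES in the pre-sharing survey.

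The Discussion states that "the present study cannot draw causal conclusions about the role of phasic and chronic processes in interpersonal emotion regulation". It adds no such reservation for the tonic claims.

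**The concern.** The wording of Hypotheses 3 and 4 makes sharing the cause of better mood and of reappraisal. The design varies only the style of sharing. The reference for both hypotheses is therefore the participant's own earlier rating, and anything else that moves ratings during a session of about two hours is included in the change.

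Several such influences are plausible here: elapsed time, habituation to the laboratory, answering the same scales again, and regression to the mean for experiences picked because they are negative.

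If the plan is followed exactly, a significant time effect or mean change would be reported as confirmation that sharing improves mood or prompts reappraisal. The design cannot support that conclusion, and the stated limitation does not withhold it.

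**Working it through.** **1. What each hypothesis is compared with**

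| Hypothesis | Reference |
|---|---|
| 1 | Randomly paired pseudo-dyads |
| 2, 5, 6 | Co-rumination against natural sharing, order counterbalanced |
| 3 | Earlier mood rating only |
| 4 | Earlier appraisal rating only |

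Among Hypotheses 1 to 6, only 3 and 4 lack a comparator. An analysis plan could not add one, because the data would not contain it.

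**2. The plan's own sample size.** For two independent groups, d = 0.5, two-sided .05 and 80% power, the t-test needs 63.77, so 64 per group and 2 × 64 = 128. The stated 128 reproduces. It refers to a two-group comparison, which Hypotheses 3 and 4 do not have.

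**3. Chance of a significant change when sharing does nothing.** Let d be a drift common to everyone, in SDs of the change score. The document gives no value, so d is assumed. For n independent units, the probability is approximately Φ(d√n − z).

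- d = 0.2, n = 150, α = .05: Φ(2.449 − 1.960) = Φ(0.489) = 0.69
- d = 0.2, n = 300, α = .05: Φ(3.464 − 1.960) = Φ(1.504) = 0.93

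The values 150 and 300 correspond to partners' changes being fully correlated or independent. With 2 × 150/(1 + ICC) effective units and an assumed ICC of 0 to 0.5, d = 0.2 gives 0.81 to 0.93. The drift needed for an 80% chance is (1.960 + 0.842)/√300 = 0.16 to (1.960 + 0.842)/√200 = 0.20 SD.

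The plan applies Bonferroni but the article does not give the number of tests. With an assumed divisor of 8, the range at d = 0.2 is 0.54 to 0.77. With an assumed divisor of 20 (α = .0025) and n = 150 to 300, it is 0.28 to 0.67. Correction makes a false claim less frequent but does not remove it, because drift is bias and not chance error.

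**4. Which tests are exposed.** A simulation of 150 couples (4,000 runs per drift value) had no sharing effect and the same drift in both conditions. Assumed variances of change were 0.3 for couple, 0.3 for person and 0.4 residual.

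| Drift (SD) | Pre-post test significant | Condition contrast significant |
|---|---|---|
| 0 | 5.2% | 4.6% |
| 0.1 | 38.5% | 4.9% |
| 0.2 | 91.1% | 5.9% |
| 0.3 | 99.9% | 5.1% |

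The condition contrast stays near 5% throughout.

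**5. Direction.** Hypothesis 4 would be supported by a detectable shift either way. For Hypothesis 3 the direction matters. In the Procedure's order, mood is rated before the negative experiences are called up. Recalling them could lower later mood, which works against the predicted improvement. If mood is instead rated in the pre-sharing survey (Table 2), the baseline comes after recall, and recovery from recall would work in favour of the hypothesis.

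**6. Interval from the ES baseline to the post-dialogue rating.** Take 60/4 = 15 minutes per dialogue slot, with the rating about 10 minutes in (2 minutes of preparation plus 8 of dialogue).

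- Procedure order, with 15 + 15 minutes before the task: 30 + 15(k − 1) + 10 = 40, 55, 70 and 85 minutes for dialogues k = 1 to 4.
- Table 2 order, ES somewhere within the 15-minute survey: about 10–25, 25–40, 40–55 and 55–70 minutes.

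The 10 minutes of task instructions are left out because their place in the sequence is unclear.

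**The case against.** Before-after predictions are common, and the stated aim is the effect of co-rumination compared with natural sharing. That contrast is counterbalanced and unaffected by a common shift. The Discussion also says that co-rumination is the one tonic process manipulated, which implies that sharing itself is not. All of this stands, and it confines the problem to Hypotheses 3 and 4. It does not remove the problem, because Table 1 still words these two causally and calls them confirmatory.

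The percentages are the ordinary power of a one-sample test against a small shift. They do not show that such a shift occurs in this study. That also stands; they show only how little drift would be enough.

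A reader might infer that any drift over the session would confirm both hypotheses. The document does not support this. Hypothesis 3 is directional, the drift must be large enough to detect, and in the Procedure's order the recall of negative experiences would tend to hide a mood benefit.

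A reader might also infer that the later dialogues exceed the article's own tonic limit of roughly one hour. For dialogue 3 this holds only under the Procedure's order; under Table 2, only dialogue 4 might exceed an hour. In any case the article uses that figure for how long the regulation process runs, not as a maximum gap between ratings.

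**Conclusion.** The point holds for Hypotheses 3 and 4 as worded. The design can show that mood and appraisal change from before to after the dialogues, but not that sharing causes the change. This follows from the Design and Tonic timescale sections without any numerical assumption.

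The size cannot be fixed from the document. The 69% to 93% at .05 rests on an assumed 0.2 SD shift and 150 to 300 independent units, and the lower figures under Bonferroni rest on assumed numbers of tests. The likely direction of bias for Hypothesis 3, and the interval over which drift could act, depend on whether the Procedure or Table 2 gives the true timing of the BEF and ES.

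It would be wrong to conclude that the study's experimental results are compromised: Hypotheses 5 and 6 are protected from a shift common to both conditions.

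**What to change.** 1. Restate Hypothesis 3 as mood being more positive after the dialogues than before, and Hypothesis 4 as appraisals of the discussed experiences differing from before to after. Extend the limitation in the Discussion: the effect of sharing itself is not identified, and only the co-rumination versus natural sharing contrast supports a causal reading. The cost is wording only, and this remains possible after data collection.

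2. Reconcile the Procedure with Table 2 on when the baseline BEF and ES are completed. This also costs only wording.

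3. Optionally, for couples still to be run, have participants also re-rate the ES for experiences not yet shared, as a supportive comparison for Hypothesis 4. Under the order in the Co-rumination manipulation section (roles switch after two rounds), this gives a within-person contrast only after dialogues 1 and 3. After dialogue 2 it gives only a between-partner contrast, with a partner who has just acted as supporter. After dialogue 4 nothing is left unshared. The shared topic also gets two minutes of preparation that the other may not. The cost is more rating burden and possible reactivity. The article gives 31/12/2024 as the end of recruitment, so this option may no longer be open.

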### Sample size determination

We determined the sample size based on a priori power analysis (G*Power) [21]. For a power of at least 80% to compare the means of two independent groups, a minimum sample size of 128 dyads is required to detect medium effects (0.5) at α < .05 for two-tailed comparisons. A minimum sample size of 59–114 dyads is required to detect small effects (0.1–0.2) at α < .05 for linear multiple regression. We aim to recruit a sample size of 150 dyads for our study, so that we will be able to accommodate potential exclusions of participants due to unforeseen reasons. Compared to other studies on synchrony [22,23], our study features a large sample size.

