#### Chronic timescale.

***Relationship quality and dyadic coping analysis:*** We will employ regression analysis to examine the associations between relationship quality and dyadic coping strategies and movement and cardiovascular synchrony (*Hypothesis 7.1 and 7.2*). Additionally, to analyse whether dyadic coping and relationship quality are associated with mood changes we will add these variables as fixed factors in the linear mixed models built for testing hypothesis 3 on mood change over time (*Hypothesis 7.3*). Linear regression analyses will also be used to assess whether relationship quality and dyadic coping are related to emotional appraisal change (*Hypothesis 7.4*).

To assess whether co-rumination versus natural sharing influences the relationship between higher relationship quality and more constructive dyadic coping and movement and cardiovascular synchrony moderated regression analyses will be used (Hypotheses 8.1 and 8.2). To analyse whether the associations between relationship quality and dyadic coping with mood change are associated with effects of co-rumination versus natural sharing we will extend the linear mixed models used for testing hypothesis 7.3. The full model will consist of a random intercept for participants, fixed factors of assessment time and condition, their interaction, and mood as the dependent variable (*Hypothesis 8.3*). Moderated linear regression analyses will be used to assess whether better relationship quality and dyadic coping are associated with weaker effects of the co-rumination condition versus natural sharing on emotional appraisal change (*Hypothesis 8.4*).

The hypotheses presented in Table 1 and the data analysis techniques utilized constitute the core elements of our research. Additionally, we have identified and measured a range of secondary variables that could potentially influence these associations. Our aim is to incorporate these variables as covariates in the analyses to enhance our understanding of the findings. For all statistical tests α ≤ 0.05 (two-tailed) will be applied. Given the wide range of statistical tests performed, there is a concern regarding multiple comparisons. Therefore, to reduce the likelihood of Type I errors, we will apply the Bonferroni correction to all previously mentioned test results.

***Exploratory analyses summary:*** In our study, we plan to conduct exploratory analyses to investigate interpersonal synchrony in verbal communication:

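### Hypothesis 5 predicts equal or better mood after co-rumination, but the plan tests only for a difference and gives no criterion for equality

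*Protocol article*

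**What the plan says.** Table 1 of the protocol article (section Proposed experiment and hypotheses) is titled "Main confirmatory hypotheses for the three timescales". Its tonic row contains Hypothesis 5 (H5): "Compared to natural sharing, co-rumination may lead to equal or even more positive mood outcomes". The prediction thus covers two outcomes, no difference and superiority of co-rumination.

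The Data analysis plan, under Tonic timescale, sets the test: "we will examine whether mood following co-rumination differs from mood following natural sharing using the same LMM framework". The outcome compared is mood after sharing. The end of the Chronic timescale section sets the error rate for every test: "For all statistical tests α ≤ 0.05 (two-tailed) will be applied". It then adds a multiplicity rule: "we will apply the Bonferroni correction to all previously mentioned test results". The number of tests is not given.

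The Sample size determination section plans for detecting a difference between two independent groups at 80% power. Its stated result is that "a minimum sample size of 128 dyads is required to detect medium effects (0.5) at α < .05 for two-tailed comparisons". The article states no margin, confidence-interval rule or other criterion by which mood in the two conditions would be judged equal.

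**The concern.** A test of difference can show that two conditions differ. If it is not significant, it has not shown that they are equal. H5 nevertheless names equality as one of its two predicted outcomes. Under the stated rules only one result clearly contradicts H5, which is significantly worse mood after co-rumination. A null result fits the wording of H5 whether the conditions are truly alike or the study was too imprecise to separate them.

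Bonferroni then works in an unusual direction. For the other hypotheses about the manipulation, such as H2 (enhanced synchrony) and H6 (smaller appraisal change), a stricter threshold makes the prediction harder to support. For H5 it makes the one contradicting result harder to reach. At stake is what a confirmatory statement about the effect of the manipulation on mood would mean. The estimate itself stays valid.

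**Working it through.** **The plan's own figure.** Two independent means, d = 0.5, two-sided 0.05, power 80%. The normal formula gives n per group = 2(1.960 + 0.842)²/0.5² = 62.8, so 63 per group and 126 in total. The exact t-test gives 63.77, so 64 per group and 128 in total. The stated 128 is reproduced. It is a sample size for detecting a difference, not for showing equality.

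**Inputs for the check.**
- N = 150 couples, the recruitment target.
- Paired comparison, because the Design section has every couple do both conditions twice. The mixed model is approximated by a paired t-test on couple-level differences.
- Effects are in standard deviations of the within-couple difference (dz). The true harm of 0.2 or 0.3 is an assumption.
- Number of tests k, not stated, so assumed: 1 (no correction); 8 (one per hypothesis); 16 (H1 and H2 for two signals each = 4, H3 to H6 = 4, H7 = 4, H8 = 4); 24 (as 16, but with relationship quality and dyadic coping tested separately in H7 and H8: 8 + 8 + 8).

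**Chance that a true harm is missed.** With α = 0.05/k, t* the two-sided critical value on 149 degrees of freedom and noncentrality λ = −dz·√150, the chance is 1 − P(T(149, λ) < −t*). For dz = 0.2, λ = −2.449; for dz = 0.3, λ = −3.674.

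| k | α | t* | missed, dz = 0.2 | missed, dz = 0.3 |
|---|---|---|---|---|
| 1 | 0.05 | 1.976 | 32% | 4.5% |
| 8 | 0.00625 | 2.774 | 62% | 19% |
| 16 | 0.003125 | 3.004 | 71% | 25% |
| 24 | 0.00208 | 3.133 | 75% | 30% |

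With 128 couples the dz = 0.2 column becomes 39%, 69%, 77% and 80%. On the independent-groups basis of the sample size section (128 in total, d = 0.2) it is 80%, 95% and 97% for k = 1, 8 and 16. In every case the miss rate rises with k.

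**What a non-inferiority rule would need.** With margin m in the same units and truly equal conditions, power = P(T(149, m√150) > t*). The noncentrality is 3.674 for m = 0.30 and 3.062 for m = 0.25. The margins are illustrative; the documents give none.

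| k | power, m = 0.30 | power, m = 0.25 |
|---|---|---|
| 1 | 95% | 86% |
| 16 | 75% | 52% |
| 24 | 70% | 47% |

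Cross-check by the normal formula for k = 16, m = 0.30, power 80%: (2.955 + 0.842)²/0.30² = 160.2, so 161 couples, just above the target of 150. A margin of 0.5 needs 58.

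**The case against.** The strongest reply is that the article never says a non-significant result will count as support. It says only that the authors will examine whether mood differs. A reader might infer that the authors have planned to declare H5 confirmed on a null result. The text does not support that inference. It supports only that such a reading is left open, because equality is a predicted outcome and nothing defines how it would be shown.

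Second, H5 is hedged, and the Introduction leans towards benefit: it expects that sharers may feel better after a single episode of co-rumination. On that reading equality is a caveat to a superiority expectation, the two-sided test is suitable and Bonferroni is conservative in the ordinary way. This is a fair reading. It shows that restating H5 as superiority would remove the mismatch. But Table 1 still classes the hypothesis as confirmatory with equality in it.

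Third, more detail on the hypotheses is referred to Supplementary 1, which was not available, and an analysis plan may exist. A criterion could be there, so its absence from the article carries limited weight. The mismatch between the stated hypothesis and the stated test does not depend on it.

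Fourth, a reader might infer that the planned sample comfortably supports a non-inferiority claim. That holds at margins of 0.25 to 0.30 only without the correction that the plan applies to all tests. Such margins would also tolerate the harm of 0.2 used above. Under that true harm, an uncorrected rule would claim at least equal mood about 9% (margin 0.25) or 23% (margin 0.30) of the time. Any margin therefore has to be justified on the mood scale.

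**Conclusion.** The point holds as a mismatch between a confirmatory hypothesis and its test. The planned test can support the superiority half of H5 or contradict H5 through significant harm. It cannot establish the equality half, and each further test in the Bonferroni family makes H5 harder to contradict. For a true harm of dz = 0.2 with 150 couples, the chance of missing it rises from 32% uncorrected to between 62% and 75% for 8 to 24 tests. At dz = 0.3 it rises from 4.5% to between 19% and 30%.

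The sizes rest on the assumed harm, the paired approximation, no loss of couples and an assumed number of tests; the direction does not. This should be corrected before analysis. It does not undermine the mixed-model estimate, and the documents do not show an intention to treat a null result as proof.

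**What to change.** State in the plan that a non-significant difference in mood does not support H5. Then choose one of two routes.

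(a) Restate H5 as superiority only and keep the planned test. This costs a change of wording and no power; the claim of equality is given up.

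(b) Keep both halves of H5. Before analysis, fix and justify a margin on the BEF (mood adjective checklist) scale. Score mood so that higher is better and take co-rumination minus natural sharing. Claim at least as positive mood only if the lower confidence limit lies above minus the margin, and more positive mood only if it lies above zero. Set the interval at the same Bonferroni-adjusted level as the other tests, which requires stating how many tests the correction covers.

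Route (b) uses the same mixed-model contrast, so the analysis itself is unchanged. Its cost is the margin justification and the loss of power shown above: at the adjusted level, 150 couples support it only for margins wider than about 0.30. Route (a) has no such cost. A margin chosen after the results are known would not be credible.
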